### Oversight and monitoring

#### Composition of the coordinating center and trial steering committee

Prior to the start of the study, the gynecologic medical team will receive formal training about the study protocol and data collection procedures. All necessary research documents will be made available to each researcher at any time. Medical researchers will supervise the screening and inclusion of patients.

The trial’s day-to-day coordination will be managed by two gynecologists and one pathologist, along with support from an epidemiologist, Trial Steering Committee overall management, monitoring, auditing, data management, statistical analysis, and writing, regularly submit progress report results twice a year.

#### Data monitoring committee

The data monitoring committee (DMC) will be composed of clinical trial specialists, including a biostatistician, who are not associated with the study. The committee will meet at least twice a year, and all data obtained from the trial will be evaluated by the committee. The DMC will review unblinded outcome data for safety and efficacy, and judge if there is evidence that either treatment is unsafe and the trial should be discontinued. The DMC will also advise the Trial Steering Committee of any evidence of unethical treatment or unacceptably serious adverse events. The IBM Clinical Development Management System (IBM Corporation, Somers, New York), which is based on an EDC (Electronic Data Capture System), will be used to manage the data in this study [19].

### Sample size

The main purpose of this study is to determine whether gasless laparoscopic radical hysterectomy (gasless TLRH) or equivalent to total abdominal hysterectomy (TARH) is effective in terms of disease-free survival at 4.5 years. If the difference in disease-free survival rate does not exceed 7%, then these two surgeries are considered equivalent.

The estimated 4.5-year disease-free survival rate of patients receiving TARH is 90%. The sample size was based on an expected disease-free survival rate of 90% in the open-surgery group at 4.5 years and a noninferiority margin of 7.2 percentage points for minimally invasive surgery, which reflected an acceptable difference in the expected survival rate of at most 8 percentage points. In previous studies involving patients with other types of cancer, a noninferiority margin of 6 to 8 percentage points has been considered to be clinically acceptable.

Based on these data, a total of 740 patients (370 in each group) will be sufficient to declare equivalence in 4.5 years of accrual and 4.5 years of follow-up, with an equivalence margin of 6% or less at 4.5 years [8].

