This proposed trial has strengths and weaknesses. A marked strength is that no high-quality studies are comparing the efficacy of gasless laparoscopic or abdominal surgery in the treatment of early cervical cancer. The current research experiments include ChiCTR2200064194, vaginal assisted single port laparoscopic radical surgery for cervical cancer using pneumoperitoneum and non-pneumoperitoneum: a prospective randomized controlled study. ChiCTR20000376, a randomized controlled study on the efficacy and safety of transumbilical single-hole laparoscopic surgery and traditional multi-hole laparoscopic surgery for cervical cancer. ChiCTR2100045060, a prospective randomized controlled study of robot and laparoscopic radical cervical cancer surgery. At present, there is no comparison of the clinical efficacy, safety, and clinical value between gasless laparoscopy and open surgery. If the outcome of gasless laparoscopy is the same as or better than open surgery, so this procedure had the advantages of all minimally invasive approaches, such as fast recovery and esthetic advantages. Strengths of our work also include its prospective design, standardized treatment protocol, and long duration of follow-up.

A limitation of this trial is that the design is not that of a confirmatory trial. Evaluation of the overall survival rate and recurrence rates, which are associated with the primary endpoint, will be performed by a clinical review board. The evaluation will be conducted under blind and independent conditions. And we will apply sensitivity analysis of per-protocol analysis to assess potential biases. Therefore, we believe that it will be possible to maintain objectivity and reduce potential bias. In addition, this is a single-center, randomized controlled trial design, although the operation is easy to operate and can be widely applied for gynecologists who have the foundation of traditional open cervical cancer surgery and laparoscopic surgery, in the future, we need multicenter, prospective studies to draw further strong conclusions.

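### The sample-size section gives conflicting margins (6%, 7%, 7.2 and 8 points) and mixes equivalence with non-inferiority; its claim that 740 patients suffice for equivalence at 6% or less is not supported on 4.5-year rates at conventional settings

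*Protocol article*

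**What the plan says.** All the figures stand in the Sample size section of the protocol article, in this order:

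- Equivalence rule: "If the difference in disease-free survival rate does not exceed 7%, then these two surgeries are considered equivalent".
- Basis of the calculation. For the control arm: "expected disease-free survival rate of 90% in the open-surgery group at 4.5 years". For the threshold, in the same sentence: "a noninferiority margin of 7.2 percentage points for minimally invasive surgery".
- Explanation of that margin: it reflected "an acceptable difference in the expected survival rate of at most 8 percentage points".
- Adequacy claim: 740 patients, 370 per group, "will be sufficient to declare equivalence in 4.5 years of accrual and 4.5 years of follow-up, with an equivalence margin of 6% or less".

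The Abstract's conclusions also speak of equivalence. The Discussion takes a one-sided view of what would favour the new operation: "If the outcome of gasless laparoscopy is the same as or better than open surgery". The Statistical analysis section names a log-rank test as the main comparison and promises a 95% confidence interval for the treatment difference, but ties neither to a margin. No alpha, sidedness, power or dropout rate is given for the sample size.

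**The concern.** A margin is the decision rule of an equivalence or non-inferiority trial. Here a reader can find 6, 7, 7.2 or 8, and can read the hypothesis as two-sided or one-sided. A result that fails under one sentence can pass under another, and nothing in the article says which governs.

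The gap matters in practice. Suppose open surgery shows 90% DFS, each arm has 370 patients, and the 95% confidence limit for the deficit must stay inside the margin. The largest observed deficit that passes is about 1.5 points at a margin of 6 and about 2.6 points at 7.2. A deficit of 2 points would succeed or fail according to the sentence applied. The Introduction cites worse survival after minimally invasive surgery as the reason for the trial, so this threshold should not be open to choice once results are known.

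The adequacy claim is attached to the strictest combination in the section, equivalence at 6% or less. That is not the margin on which the section says the size was based.

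**Working it through.** **Inputs.** From the Sample size section: open-arm DFS of 90% at 4.5 years, 370 per arm, margins m of 6, 7, 7.2 and 8 points. Assumed, because not stated: 90% DFS in the new arm too (true difference zero), no losses, alpha of 2.5% or 5% per side, power of 80% to 90%. The 95% interval in the Statistical analysis section would correspond to 2.5% per side.

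**Formulas for 4.5-year rates**

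- SE = √(2 × 0.9 × 0.1 / 370) = 0.02206
- Non-inferiority power = Φ(m/SE − z_α)
- Equivalence power (two one-sided tests) = 2Φ(m/SE − z_α) − 1
- n per arm = (z_α + z_β)² × 0.18 / m²; for equivalence, β is replaced by β/2

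**Reproducing 740.** At 7.2 points, one-sided 2.5% and 90% power: (1.960 + 1.282)² × 0.18 / 0.072² = 364.9, so 365 per arm and 730 in total. Equivalence at 2.5% per side and 80% power uses the same z values and also gives 730. Other settings come close too:

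- Equivalence at 7.2 points, 5% per side, 90% power: 752.
- Equivalence at 8 points, 2.5% per side, 90% power: 366 per arm, 732.
- Non-inferiority at 7 points, one-sided 2.5%, 80% power, variance taken at 90% and 83%: 742.
- Non-inferiority at 6 points, one-sided 5%, 85% power: 720.

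So 740 is compatible with 7.2 points, but the number alone does not identify the design.

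**Power with 370 per arm**

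| Margin | Non-inferiority, 2.5% | Non-inferiority, 5% | Equivalence, 2.5% per side | Equivalence, 5% per side |
|---|---|---|---|---|
| 6 | 78% | 86% | 55% | 72% |
| 7 | 89% | 94% | 77.5% | 87% |
| 7.2 | 90% | 95% | 81% | 89.5% |
| 8 | 95% | 98% | 90% | 95% |

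For example, at 6 points 0.06/0.02206 = 2.720. Then 2.720 − 1.960 = 0.760, Φ = 0.776, and 2 × 0.776 − 1 = 0.55.

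**Total needed at 6 points**

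| | 80% power | 90% power |
|---|---|---|
| Equivalence, 5% per side | 858 | 1084 |
| Equivalence, 2.5% per side | 1052 | 1300 |
| Non-inferiority, one-sided 5% | 620 | 858 |
| Non-inferiority, one-sided 2.5% | 786 | 1052 |

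**Losses.** With an assumed 10% lost (333 per arm), SE = √(0.18/333) = 0.02326. Non-inferiority power at 7.2 points is then Φ(0.072/0.02326 − 1.960) = 87%.

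**Observed deficit that passes.** Solve d + 1.96 × √{[0.9 × 0.1 + (0.9 − d)(0.1 + d)]/370} = m. At d = 0.0153 the left side is 0.060; at d = 0.0264 it is 0.072.

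**The case against.** The strongest reply is that, without alpha or power, the protocol cannot be shown to be under-sized. Much of that stands. A reader might infer that 740 is simply too few for 6 points, but a one-sided 5% non-inferiority test at 6 points has 86% power.

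The main comparison is also a log-rank test, not a comparison of rates. Six points corresponds to a hazard ratio of ln 0.84 / ln 0.90 = 1.655. If DFS is exponential and every patient is followed to study end (4.5 to 9 years), about 108 events arise and one-sided power is 83% at 5% and 74% at 2.5%. If 6 points in the other direction is translated the same way (96% against 90%), the second equivalence test costs almost nothing on that scale; with symmetric hazard-ratio limits, equivalence power falls to 67% at 5% per side. However, Study assessments and procedures ends each patient's visits at year 4.5. Counting events only to then leaves 74 events, and one-sided power of 70% and 58%.

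Two other stronger readings also fail. A reader might infer that 370 per arm fits 7.2 points alone, but the near matches above rule that out; what singles out 7.2 is the text naming it as the basis. A reader might also take the 8 as a mislabelled relative figure, since 0.08 × 90 = 7.2. That is plausible, and the 8 would then be the source of the 7.2 and not a separate margin, but the text calls it percentage points and does not say so. The conflict between 6, 7 and 7.2 would remain.

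Finally, the Discussion sentence is about potential advantages and is not a decision rule, so it adds little to the contradiction within Sample size.

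**Conclusion.** The contradiction is certain and needs no assumption: one section gives incompatible margins and two hypothesis types, and nothing elsewhere in the article resolves them. The phrase about 6% or less does not even fix a single value, and any smaller margin needs more patients.

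The numerical conclusion is conditional. With 90% DFS in both arms and no losses, 740 patients give 55% to 72% power for equivalence at 6 points on 4.5-year rates. The claim of sufficiency is therefore not supported there at 2.5% or 5% per side and at least 80% power. A true deficit in the new arm, or losses, would lower the power further. The documents do not support a flat statement that 740 is inadequate under every design. Nor do they show that the trial was planned for 90% power at one-sided 2.5%, since 80% equivalence power at 2.5% per side gives the same 730.

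**What to change.** Before any comparison of outcomes by arm, and decided by people who have not seen such data, state one hypothesis type and one margin in percentage points. Use them in the objective, the sample size and the Abstract's conclusions. Add alpha, sidedness, and the power that 740 delivers.

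- **If the stated basis is kept:** non-inferiority at 7.2 points, about 90% power at one-sided 2.5% before losses and about 87% with 10% lost (an assumed rate). Delete the 6%, 7% and 8-point statements, or explain the 8 if it is the relative figure behind 7.2. Replace equivalence by non-inferiority.
- **If 6 points is kept with 740 patients:** replace the claim of sufficiency by the power on 4.5-year rates, 55% to 72% for equivalence or 78% to 86% for non-inferiority, according to the alpha chosen.
- **If equivalence at 6 points with 80% power is required:** 858 patients (5% per side) or 1052 (2.5% per side), which is 118 or 312 more than planned.

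The first two options cost only wording, plus a stated claim less favourable than equivalence at 6% or less. The third costs recruitment. The choice and its justification belong to the sponsor.

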### Recruitment

Eligible patients will be continuously recruited until the target sample size is reached. Investigators of participating hospitals identified potential trial participants from routine medical practice. All outpatients were asked if they wanted to participate when they were told that they were getting an operation. We will recruit 740 participants over 5 years.

### Statistical analysis

The main endpoint will be analyzed based on the intention-to-treat principle.

#### Phase 1 analysis (feasibility pilot)

After accumulating 100 patients, the data will be analyzed to determine several key points and analysis of surgical safety.

A research component that is not the primary endpoint specified in the protocol. These will include:Accrual rateCompliant with randomized treatment allocation

If these components are satisfactory, the Test Management Committee will make a decision to proceed.

In the second stage, 740 patients will receive complete therapy.

#### Phase II analysis (phase III study)

The disease-free survival and overall survival curves will be estimated using the Kaplan–Meier method. The main comparison of survival distribution will be compared with the logrank test. The secondary analysis will use appropriate regression models (such as Cox proportional risk models) to adjust for prognostic factors. All efficacy indicators will be compared through intention-to-treat analysis, including all randomized patients. The toxicity will be analyzed based on the treatment received. The difference between treatment groups will be reported with a 95% confidence interval.

Descriptive statistics on treatment-related adverse events and quality of life (FACT-Cx, SF-12). At each evaluation, subscales (Physical Health, Social Health, Emotional Health, Functional Health, Cervical Cancer Specific Health, and Body Image Scale) will be calculated for each random group.

Similarly, descriptive statistics will be calculated for other results, such as pain score, anxiety and depression score, Analgesic consumption, etc.

The normality of continuous variables and the equality of inter-group variance will be evaluated.

Discrete variables (such as the presence/absence of postoperative infection) will be summarized as follows frequency/proportion.

For continuous variables, analysis of variance and/or regression analysis will be used where appropriate. If the assumptions of these tests are violated, alternative non-parametric tests will be used. Differences between groups with respect to discrete variables will be assessed using the chi-squared test.

Exploratory analysis adjusts prognostic factors including age, tumor size, staging, and tumor grading.

Differentiation, depth of muscle invasion, lymph node involvement, treatment type, and ECOG status will be evaluated using proportional risk regression methods. The impact of baseline quality of life on survival will also be studied.

We will analyze the results related to treatment costs based on different surgical methods [8].

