**Method and design:**

This will be an open-label, 2-armed, randomized, phase-III single-center trial of comparing laparoscopic radical hysterectomy based on open state with abdominal radical hysterectomy in patients with early-stage cervical cancer. A total of 740 participants will be randomly assigned into 2 treatment arms in a 1:1 ratio. Clinical, laboratory, ultrasound, and radiology data will be collected at baseline, and then at the study assessments and procedures performed at baseline and 1 week, 6 weeks, and 3 months, and follow-up visits begin at 3 months following surgery and continue every 3 months thereafter for the first 2 years and every 6 months until year 4.5. The primary aim is the rate of disease-free survival at 4.5 years. The secondary aims include treatment-related morbidity, costs and cost-effectiveness, patterns of recurrence, quality of life, pelvic floor function, and overall survival.

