**Conclusions:**

This prospective trial aims to show the equivalence of the laparoscopic cervical cancer surgery in the open state versus the transabdominal radical hysterectomy approach for patients with early-stage cervical cancer following a 2-phase protocol.

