### Methods for additional analyses (e.g., subgroup analyses)

Subgroup analyses will not be conducted. However, we will apply sensitivity analysis of per-protocol analysis to assess potential biases.

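### The main comparison is a logrank test of equality, and no confidence limit is tied to a margin, so the stated analysis cannot support the equivalence or non-inferiority claim on 4.5-year DFS

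*Protocol article*

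**What the plan says.** **Aim.** The abstract's conclusions state: "This prospective trial aims to show the equivalence of the laparoscopic cervical cancer surgery in the open state". The endpoint is a rate at a fixed time: "The primary aim is the rate of disease-free survival at 4.5 years".

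**Main test.** Under the Phase II analysis heading: "The main comparison of survival distribution will be compared with the logrank test". DFS curves are to be estimated by Kaplan–Meier, Cox models are secondary, and the group difference is to be reported with a 95% confidence interval. That section mentions no margin.

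**When equivalence is concluded.** The only such sentence is in the Sample size section: "If the difference in disease-free survival rate does not exceed 7%, then these two surgeries are considered equivalent". The same section also gives "a noninferiority margin of 7.2 percentage points for minimally invasive surgery" and "an acceptable difference in the expected survival rate of at most 8 percentage points", and it attaches an equivalence margin of 6% or less to the 740 patients. It states no alpha, sidedness or power.

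**Analysis set.** "The main endpoint will be analyzed based on the intention-to-treat principle"; for the per-protocol set, "we will apply sensitivity analysis of per-protocol analysis to assess potential biases".

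**The concern.** The hypothesis tested is not the hypothesis claimed. A logrank test asks whether two whole curves are equal. Rejection shows a difference. Non-rejection may mean that the curves are close or that there were too few events to separate them, and having fewer events makes non-rejection easier. The test takes no account of how large a deficit would be acceptable or of what happens at 4.5 years.

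The 7% sentence does not fill the gap, because it refers to a difference without saying how uncertainty in that difference is handled. The 95% interval could do so, but no section says which limit must exclude which margin.

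The error at stake is to call the new operation equivalent when it is worse by the full margin. The Introduction itself reports higher recurrence and mortality for minimally invasive surgery in the earlier randomized trial, so this is the direction of error that the primary analysis most needs to control.

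**Working it through.** **Inputs from the protocol article:** 370 per arm, 1:1 allocation, 90% control DFS at 4.5 years, and candidate margins of 6, 7, 7.2 and 8 points (Sample size).

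**Assumed, because not stated:** no dropout; one-sided 2.5% for the interval rule; two-sided 5% for the logrank test; exponential DFS times for the logrank figures.

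**1. The plan's own figure.** Non-inferiority sample size per arm with equal true rates is n = (1.960 + z_power)² × 2 × 0.9 × 0.1 / margin².
- Margin 7.2 points, 90% power: (1.960 + 1.282)² × 0.18 / 0.072² ≈ 365 per arm, 730 in total, close to 740.
- Margin 6 points: 786 in total at 80% power and 1,052 at 90%.

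The 740 therefore cannot be reproduced from stated inputs alone. It fits a one-sided margin of 7.2 points at 2.5% and 90% power, but not the 6% margin attached to it under those settings.

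**2. If the 7% rule were applied to the observed difference.** P(declare) = Φ((0.07 − d)/SE), with SE = √[0.09/370 + (0.9 − d)(0.1 + d)/370].
- d = 7 points: SE = 0.0250, P = 50%
- d = 7.2 points: SE = 0.0251, P = 47%
- d = 8 points: SE = 0.0253, P = 35%

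A simulation of 20,000 trials gave 49%, 46% and 33%. The 50% at the boundary holds for any sample size. An observed deficit of exactly 7 points has an upper 95% limit of 7 + 1.96 × 2.50 ≈ 11.9 points.

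**3. If a non-significant logrank test were read as equivalence.** The hazard ratio at a 7.2-point deficit is ln(0.828)/ln(0.9) = 1.79. P(non-significant) = 1 − Φ(√(D/4) × ln(1.79) − 1.96), where D is the number of events.
- Follow-up to 4.5 years each: D = 370 × (0.10 + 0.172) ≈ 101, P ≈ 17% (simulation 18%).
- Uniform accrual over 4.5 years with everyone followed to year 9: D ≈ 145, P ≈ 6%.

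The assessment schedule ends at year 4.5, which favours the first event count. The accrual and follow-up periods in the Sample size section allow the second. The error rate follows the event count and is not fixed by alpha.

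**4. A confidence-limit rule on the same 740 patients.** Non-inferiority is claimed only if the upper 95% limit for the deficit at 4.5 years lies below the margin.
- At 7.2 points, the simulated false-claim rate at a true 7.2-point deficit is 2.6%. The rule needs an observed deficit of about 2.6 points or less: with SE evaluated at that deficit, 2.6 + 1.96 × 2.33 ≈ 7.2.
- With no true difference SE = √(0.18/370) = 0.0221, and power is Φ(margin/SE − 1.96) for non-inferiority or 2Φ(margin/SE − 1.96) − 1 for two-sided equivalence:

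| Margin (points) | Non-inferiority | Equivalence |
|---|---|---|
| 6 | 78% | 55% |
| 7 | 89% | 78% |
| 7.2 | 90% | 81% |
| 8 | 95% | 90% |

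**The case against.** **The text is close to a valid rule.** It has a fixed-time endpoint, Kaplan–Meier estimation, a non-inferiority margin and a 95% interval for the difference. What is missing is the sentence joining them, and an unseen analysis plan might supply it. This bears on how easy the repair is. It does not remove the point, because the article names the logrank test as the main comparison and any later plan would have to override that. Nor can the reader supply the link, since four values compete for the margin.

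**The article does not say that the observed difference is what must stay within 7%.** A reader might infer this, but the word is absent. The sentence sits in the Sample size section and can be read as defining a margin for the true difference. The 50% and 47% figures hold only on the first reading. On the second, the article has no decision rule at all beyond a test that cannot support the claim.

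**The article nowhere says that a non-significant logrank result means equivalence.** The 17% and 6% show what would follow if it were used that way; they are not error rates that the plan has adopted. Likewise, 2.5% is a conventional benchmark and not a stated intention.

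**Intention-to-treat.** A reader might go further and hold that an intention-to-treat decision set hides a deficit through dilution. The documents do not support this. The rule on abandoning hysterectomy is worded the same for both arms, no rate of non-receipt is given, and a per-protocol sensitivity analysis is already planned. Requiring both analyses to agree is a debatable design choice and not the correction of an error.

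**Conclusion.** The point stands on the wording of the article and needs no calculation: the main test has equality as its null, uses neither margin nor time point, and no confidence limit is compared with a margin. Carried out as written, the primary analysis cannot establish equivalence or non-inferiority. It should be corrected before any outcome analysis, because it governs the trial's main conclusion.

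The size depends on how the gap is filled in practice. False equivalence would occur in 47% to 50% of trials at a true deficit of 7.2 to 7 points under a point-estimate rule. It would occur in about 6% to 17% at 7.2 points if logrank non-significance were used, depending on follow-up. These figures rest on 370 per arm, 90% control DFS and no dropout; the logrank figures also assume exponential times. They do not show that the sponsor intends either rule.

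**What to change.** 1. State one hypothesis, non-inferiority or equivalence, and one margin, reconciling the 6, 7, 7.2 and 8 in the Sample size section. Choosing one-sided non-inferiority would change the aim stated in the abstract, and this should be said openly.
2. Make the primary analysis the difference in Kaplan–Meier DFS at 4.5 years (gasless minus open) with a two-sided 95% confidence interval. Claim non-inferiority only if the lower limit lies above minus the margin; if equivalence is kept, require both limits to lie within the margin.
3. Make the logrank test and Cox model supportive.
4. Reword the 7% sentence so that it refers to the confidence limit.
5. State alpha and the resulting power for the chosen hypothesis and margin.
6. Keep the per-protocol analysis as the planned sensitivity analysis.

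**Cost.** The change is one of wording and needs no new data. Whether 740 patients remain enough depends on the choice in step 1: power is about 90% for non-inferiority at 7.2 points, but about 78% at 6 points and 55% for two-sided equivalence at 6 points. Close results that might have been called equivalent would become inconclusive.

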### Inclusion criteria

Age ≥ 18 yearsAdenocarcinoma, squamous cell carcinoma, or adenosquamous carcinoma of the cervixECOG performance status of 0–1FIGO (2018) clinical stage IA1 disease with lymphovascular space invasion, IA2 disease, or IB1 disease (< 2 cm and limited to the cervix)Patients could undergo either a type II or a type III radical hysterectomy (Piver classification) and pelvic lymphadenectomyPostoperative adjuvant radiation therapy was recommended according to the Sedlis criteria, which are widely accepted [18]

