### Baseline assessments

Baseline assessments will be performed according to the trial standard operating procedure (SOP), including medical history, determination of BMI, CT and MRI imaging, blood tests, and cervical tissue specimens will be obtained by treating gynecologic oncologists. Histopathological examination of tissue specimens will confirm the cell type and grade of differentiation [19].

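### Adjustment for baseline prognostic factors is confined to a secondary Cox model, so it adds no precision to the 4.5-year DFS difference held against the margin; the gain forgone is real but small.

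*Protocol article*

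**What the plan says.** The Phase II analysis section of the protocol article fixes an order of analyses. The main one is a log-rank test: "The main comparison of survival distribution will be compared with the logrank test". Adjustment ranks below it: "The secondary analysis will use appropriate regression models (such as Cox proportional risk models) to adjust for prognostic factors". The same section then gives an exploratory list, "Exploratory analysis adjusts prognostic factors including age, tumor size, staging, and tumor grading", followed by a further sentence: "Differentiation, depth of muscle invasion, lymph node involvement, treatment type, and ECOG status will be evaluated using proportional risk regression methods". It promises a 95% confidence interval for the treatment difference but names no estimator.

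The decision itself is set on another scale. The Sample size section compares 4.5-year DFS rates in percentage points, with 90% expected after open surgery and, in one of its statements, "a noninferiority margin of 7.2 percentage points for minimally invasive surgery".

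The baseline data exist. Table 1 schedules clinical staging, CT and MRI, cervical biopsy and ECOG before surgery. Under Baseline assessments the plan adds: "Histopathological examination of tissue specimens will confirm the cell type and grade of differentiation".

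**The concern.** Whether the new operation is accepted depends on where the confidence limit for the 4.5-year DFS difference falls. That depends in part on how wide the interval is. Adjusting for prognostic factors known before randomisation narrows the interval somewhat and offsets chance imbalance in those factors. If the adjusted result is averaged over the trial population, the question asked stays the same.

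As written, the plan cannot collect this benefit. The log-rank test uses no covariates. The only adjusted model named for DFS gives a conditional hazard ratio, and that is not the quantity compared with the margin. What is at stake is a little power and some protection against chance imbalance, not the validity of the result.

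**Working it through.** **Inputs from the documents.** 370 per arm; 90% DFS at 4.5 years with open surgery; margin 7.2 points (6 is also stated); 95% CI.

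**Assumptions.** 90% DFS in the gasless arm too; complete follow-up to 4.5 years; one-sided 2.5%, read from the 95% CI. The article states neither alpha nor power.

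**1. The plan's own figure.** n per arm = 2 × 0.9 × 0.1 × (1.960 + 1.282)² / 0.072² ≈ 365, or 730 in total. This is close to the stated 740, but only with an assumed 90% power. Other assumed combinations also come close, so this is a plausible reading and not a confirmation.

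**2. Unadjusted precision at 370 per arm.**
- SE = √(2 × 0.9 × 0.1 / 370) = 2.206 points
- 95% CI half-width = 1.96 × 2.206 = 4.32 points
- Power at 7.2 points = Φ(7.2/2.206 − 1.96) = Φ(1.304) = 90.4%
- Power at 6 points = Φ(6/2.206 − 1.96) = Φ(0.760) = 77.6%
- Expected events = 740 × 0.10 = 74

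**3. Effect of adjustment.** Adjusted SE = 2.206 × √(1 − R²). Here R² is the variance of predicted risk divided by 0.1 × 0.9, for a normally distributed baseline score in a logistic model calibrated to 10% events. The documents give no prognostic strength, so a range is shown:

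| Assumed joint c-statistic | Variance reduction | SE (points) | Half-width (points) | Power at 7.2 | Power at 6 |
|---|---|---|---|---|---|
| none | 0 | 2.206 | 4.32 | 90.4% | 77.6% |
| 0.60 | 1.2% | 2.193 | 4.30 | 90.7% | 78.1% |
| 0.64 | 2.3% | 2.180 | 4.27 | 91.0% | 78.6% |
| 0.70 | 5.2% | 2.147 | 4.21 | 91.8% | 79.8% |
| 0.75 | 9.2% | 2.102 | 4.12 | 92.9% | 81.5% |

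In patients, 740/(1 − 0.0118) = 749 and 740/(1 − 0.0523) = 781, so c = 0.60 to 0.70 is worth about 9 to 41 extra patients.

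If the claim is two-sided equivalence, a word the article also uses, power at 7.2 points is 2 × 0.9039 − 1 = 80.8% unadjusted. It becomes 2 × 0.9072 − 1 = 81.4% at c = 0.60 and 2 × 0.9182 − 1 = 83.6% at c = 0.70.

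**4. The cost of fitting.** The table treats the covariate effects as known. Simulated trials of 740 patients with seven fitted covariates (6,000 per setting, standardised logistic difference) gave variance reductions of 0.9% at c = 0.64, 4.8% at c = 0.70 and 7.6% at c = 0.75. Each is below its theoretical value of 2.3%, 5.2% and 9.2%, but no setting showed a loss.

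**5. Where in the range.** Eligibility limits the spread of the strongest candidates: "IA1 disease with lymphovascular space invasion, IA2 disease, or IB1 disease (< 2 cm and limited to the cervix" for stage and size, and ECOG 0–1. That points to the lower end.

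**The case against.** The strongest reply is that an unadjusted primary analysis with an adjusted secondary one is standard and valid. Randomisation makes the comparison unbiased, and the confidence interval already allows for chance imbalance. This stands. A reader might infer from the log-rank choice that the primary result would be biased; nothing in the document supports that.

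A reader might also infer that the plan ignores its prognostic factors, or that it calls histology and ECOG prognostic. It does neither. Adjustment is planned, at a lower rank. Histology is in neither list, though cell type is confirmed at baseline. ECOG appears only in the sentence about factors to be evaluated, beside surgical findings. Only age, tumour size, stage and grade are plainly called prognostic.

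It can also be said that the estimator and covariate list belong in a statistical analysis plan, which is not shown. That holds for the detail. It does not remove the order of analyses that the article fixes. Nor does the Randomization section's silence on stratification show that none is used, so no weight is put on it here.

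Finally, the gain is neither large nor quite free. Larger figures, such as the 9% at c = 0.75, need a prognostic strength that nothing in the documents supports. A six-factor list including histology and ECOG would mean about eight or nine parameters on 74 events. Both objections stand, and they limit the size of the point and the length of the list.

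**Conclusion.** The point holds as a modest efficiency improvement. Factors that the plan names as prognostic, and that can be measured before surgery, do not reach the quantity on which the decision rests. For an assumed c-statistic of 0.60 to 0.70 the loss is about 1% to 5% of variance, 0.02 to 0.11 points of half-width, and 0.3 to 1.4 percentage points of power at 7.2 points, less what is spent on fitting. The figures rest on 90% DFS in both arms, complete follow-up and one-sided 2.5%; the prognostic strength is an assumption throughout.

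It ranks below two other matters: a log-rank test does not address a percentage-point margin at all, and the Sample size section gives several margins (6%, 7%, 7.2 points, at most 8 points). Since the first of these means that an estimator of the difference has to be specified anyway, the adjustment can be settled in the same step.

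**What to change.** In the Phase II analysis section, prespecify the primary result as the difference in 4.5-year DFS with its 95% CI, estimated with adjustment for baseline values. Either average the predicted 4.5-year DFS under each arm over all randomised patients, from a survival model, or use pseudo-observation regression.

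- Covariates: age, clinical tumour size, clinical stage with sparse levels combined, and biopsy grade, all as recorded before randomisation. State how each is coded.
- Leave out surgical findings such as invasion depth and nodal status.
- Prespecify the model form, the handling of censoring and the variance estimator.
- Hold this adjusted difference against the margin, once a single margin is settled. Keep the unadjusted Kaplan–Meier difference as a sensitivity analysis.

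The Cox model can stay as a secondary analysis. The cost is slightly more programming and model specification; no patients, visits or data are added. It should be fixed before outcome data by arm are seen.
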